# A randomized, open-label, adaptive, proof-of-concept clinical trial of modulation of host thromboinflammatory response in patients with COVID-19: the DAWn-Antico study

**DOI:** 10.1186/s13063-020-04878-y

**Published:** 2020-12-09

**Keywords:** COVID-19, SARS-CoV-2, Low molecular weight heparins, Aprotinin, Anakinra, Thromboinflammatory response, Thrombosis, Inflammation

## Abstract

**Background:**

The peak of the global COVID-19 pandemic has not yet been reached, and many countries face the prospect of a second wave of infections before effective vaccinations will be available. After an initial phase of viral replication, some patients develop a second illness phase in which the host thrombotic and inflammatory responses seem to drive complications. Severe COVID-19 disease is linked to high mortality, hyperinflammation, and a remarkably high incidence of thrombotic events. We hypothesize a crucial pathophysiological role for the contact pathway of coagulation and the kallikrein-bradykinin pathway. Therefore, drugs that modulate this excessive thromboinflammatory response should be investigated in severe COVID-19.

**Methods:**

In this adaptive, open-label multicenter randomized clinical trial, we compare low molecular weight heparins at 50 IU anti-Xa/kg twice daily—or 75 IU anti-Xa twice daily for intensive care (ICU) patients—in combination with aprotinin to standard thromboprophylaxis in hospitalized COVID-19 patients. In the case of hyperinflammation, the interleukin-1 receptor antagonist anakinra will be added on top of the drugs in the interventional arm. In a pilot phase, the effect of the intervention on thrombotic markers (D-dimer) will be assessed. In the full trial, the primary outcome is defined as the effect of the interventional drugs on clinical status as defined by the WHO ordinal scale for clinical improvement.

**Discussion:**

In this trial, we target the thromboinflammatory response at multiple levels. We intensify the dose of low molecular weight heparins to reduce thrombotic complications. Aprotinin is a potent kallikrein pathway inhibitor that reduces fibrinolysis, activation of the contact pathway of coagulation, and local inflammatory response. Additionally, aprotinin has shown in vitro inhibitory effects on SARS-CoV-2 cellular entry. Because the excessive thromboinflammatory response is one of the most adverse prognostic factors in COVID-19, we will add anakinra, a recombinant interleukin-1 receptor antagonist, to the regimen in case of severely increased inflammatory parameters. This way, we hope to modulate the systemic response to SARS-CoV-2 and avoid disease progressions with a potentially fatal outcome.

**Trial registration:**

The EU Clinical Trials Register 2020-001739-28. Registered on April 10, 2020.

**Supplementary information:**

The online version contains supplementary material available at 10.1186/s13063-020-04878-y.

Role of sponsor {5c}	The sponsor was represented in the steering committee. They had full insight into the design, collection, management, analysis and interpretation of data.

## Introduction

### Background and rationale {6a}

COVID-19 (coronavirus disease-19) has caused a pandemic with an enormous burden for healthcare systems worldwide [1]. In the absence of immunity, a large part of the world’s population remains at risk for infection during a second wave until large-scale vaccination programs become available. Although SARS-CoV-2 causes little symptoms in many patients, a subset of patients develops an aggressive disease course characterized by severe pulmonary involvement and a high mortality [2]. In these patients with severe COVID-19 disease, hyperinflammation is prominent with an important involvement of the kallikrein-bradykinin and contact pathway [3–6]. Internalization of SARS-CoV-2 (severe acute respiratory syndrome coronavirus 2) involves binding to the ACE2 (angiotensin-converting enzyme 2) receptor, which is abundantly expressed in the respiratory epithelium [7, 8]. ACE2 has local anti-inflammatory functions by inactivating kallikreins and bradykinins. A loss of ACE2 function can lead to an overactivation of the kallikrein-bradykinin pathway with pulmonary inflammation and edema [9].

Moreover, the kallikrein-bradykinin system is closely linked to the contact pathway of the coagulation system via activation of factor XII, leading to local fibrin deposition, as well as diffuse intravascular coagulation (Fig. 1) [10]. D-dimers, which are a marker for hyperfibrinolysis and high ferritin and LDH levels, predict a poor outcome in COVID-19 [2, 3]. There is also increasing evidence that drugs influencing these pathways may lead to improved outcomes [11–13]. These observations provide a proof-of-concept for our current trial in which we want to target this presumably excessive thromboinflammatory response with aprotinin, low molecular weight heparins (LMWHs), and anakinra.

**Fig. 1 Fig1:**
[figure not shown]
Effect of the investigated drugs on the pathways that are implicated in COVID-19

Specific inhibitors of the bradykinin-receptor are currently not available. However, kallikrein activity is strongly suppressed by aprotinin with a much higher affinity than tranexamic acid [14]. Aprotinin can also inhibit the protease activity of TMPRSS2 [15, 16]. Treatment of hypercoagulability, a hallmark of severe COVID-19, with LMWH is associated with increased survival compared to patients who did not receive anticoagulation in a recent study [12, 13]. Anakinra can modify hyperinflammation by inhibition of IL-1 and has been associated with potential benefit in non-randomized studies in patients with severe COVID-19 [17, 18].

Taken together, our trial consists of a unique approach based on the pathophysiology of COVID-19. There is thus a rationale for testing drugs explicitly targeting the thromboinflammatory response on multiple levels and evaluating the effect on biochemical markers, such as D-dimers, and clinical outcome.

### Objectives {7}

The study objectives are adapted from the WHO master protocol that was proposed to streamline interventional studies in patients with COVID-19 [19, 20]. The overall objective of the DAWn study is to evaluate the clinical efficacy and safety of investigational therapeutic agents relative to the standard of care in patients hospitalized with COVID-19. Additionally, the effect of interventions targeting the host response modulation will be evaluated separately in a pilot phase by a primary laboratory endpoint (change in thromboinflammatory biomarkers), and clinical outcomes will be evaluated as a secondary outcome.

Secondary objectives are to evaluate the clinical efficacy of different investigational therapeutics as compared to one another or the control arm.

All DAWn studies will investigate the same primary and secondary endpoints, listed in the full protocol available in an appendix to this paper. The primary endpoint is time to sustained clinical improvement, defined as a sustained 2-point improvement on the 7-rank WHO clinical status scale (see appendix). The essential endpoints are summarized below:
Clinical severity defined as the time from day 0 to sustained clinical improvement (improvement of > 2 points vs. the highest value of days 0 and 1 and sustained for at least 3 days) or live discharge, whichever comes firstHost thromboinflammatory status (DAWn-Antico): D-dimer levels, CRP, ferritin, LDH levels, and interleukin profileOxygenation: incidence, duration, and oxygenation-free daysMechanical ventilation: incidence, duration, and ventilator-free daysHospitalization: duration, time to live after dischargeMortality (day 15, day 28, time to death)Safety of the interventions: serious adverse events (SAEs) and adverse events (AEs) graded as severe, discontinuation or temporary suspension of drug administration (for any reason), changes in laboratory parameters (complete blood count, renal and liver function)

### Trial design {8}

This study is part of the larger DAWn consortium. The DAWn-Antico study is an adaptive, randomized, parallel-group open-label multicenter clinical trial to evaluate the safety and efficacy of promising agents in hospitalized adult patients diagnosed with COVID-19. The study is a phase 2 proof-of-concept multicenter trial program in patients with COVID-19. The adaptive study design of DAWn allows for the addition of new treatment and strata during the study based on the most updated information.

With a 2:1 randomization, the DAWn-Antico study evaluates standard thromboprophylaxis (low molecular weight heparin (LMWH) at 50 IU/kg once daily in hospitalized patients and twice daily in patients on intensive care units) with a multi-step antithrombotic and anti-inflammatory strategy (Fig. 2). This strategy consists of the following:
A.A higher prophylactic dose of subcutaneous LMWH: 50 IU/kg twice daily in hospitalized patients and 75 IU/kg twice daily in patients on intensive care units from day 0 to 15, ANDB.Aprotinin 2 × 10^6^ KIE 4 times per day as intravenous (IV) infusion from day 0 to 3 for a total of 72 h (3 × 4 doses)C.Additionally, patients with biochemical signs of hyperinflammation at baseline or during follow-up will receive add-on interleukin-1 receptor blockage by anakinra 100 mg 4× daily. Hyperinflammation is defined as an absolute lymphocyte count < 1000 cells/mL and two of the following: (1) ferritin > 800 ng/mL, (2) LDH > 400 U/L, or (3) D-dimers > 1000 ng/mL.

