### Strategies to improve adherence to interventions {11c}

For each drug, SOPs were created. Detailed information on administration is provided within the hospital’s electronic system and is displayed when nurses administer the drugs. Permanent remote assistance is available as investigators are on standby 24 h a day, 7 days a week.

Investigators and clinical trial assistants (CTAs) will monitor drug administration daily. Remarks or problems with administration, which did not need telephonic assistance, can be marked via the electronic system. Per protocol, laboratory tests will be evaluated daily. Based on these assessments, some patients will be started on anakinra when criteria are met.

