### Outcomes {12}

The study outcomes are based on the WHO master protocol, which has been proposed for all COVID-related research by the WHO [19, 20]. The ordinal scale below has also been used in multiple other COVID-19 studies [24, 25]. All outcomes will be presented overall as well as separately for patients with mild/moderate vs. severe disease at baseline.

Pilot phase of DAWn-Antico:

We will conduct a pilot phase with a pilot phase-specific primary endpoint analysis of D-dimer levels measured on day 6.

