## Statistical methods

### Statistical methods for primary and secondary outcomes {20a}

#### Analysis of the primary efficacy endpoint

The primary endpoint will be analyzed using competing risk analyses whereby death without any improvement will be considered as a competing risk. Event rates will be estimated using cumulative incidence functions (CIF). Median times to improvement will be calculated by the treatment group.

The effect of treatment will be assessed by performing a Fine and Gray competing risk regression model that includes the baseline clinical status value on day 0 as a covariate and randomized treatment as a factor. From the Fine and Gray model, the treatment effect and associated 95% confidence interval will be estimated.

In the pilot phase of DAWn-Antico, the effect of modulation of thromboinflammation will be evaluated on a laboratory primary efficacy endpoint, mean D-dimer level at day 6. The null hypothesis being tested is that the mean D-dimer level on day 6 is the same for the standard of care and intervention arm. Means will be compared with appropriate statistical testing after checking for normality. The full statistical analysis plan will be finalized before the database lock.

To evaluate the effect of aprotinin and high-dose enoxaparin vs. anakinra, analyses will be performed separately in patients with or without signs of hyperinflammation (i.e., with or without an indication for anakinra in the intervention group).

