#### Analysis of the secondary endpoint(s)

Cumulative clinical status up to day 15 will be analyzed using a general linear model adjusted for clinical status on day 0. The treatment effect will be estimated by the difference of mean values between the groups.Cumulative clinical status recorded daily during the hospital stay and on days 15 and 19 will be analyzed using a proportional odds logistic regression model, adjusted for clinical status on day 0. The common odds ratio will estimate the treatment effect.All-cause mortality rates will be estimated by the treatment group using the Kaplan-Meier method. The resulting Kaplan-Meier curves will be compared using a log-rank test. The treatment effect will be estimated by the hazard ratio using a Cox regression.Time-to-event parameters with competing risk (time to clinical improvement, composite cardiac endpoint): event rates will be estimated using cumulative incidence functions (CIF), and the resulting CIF curves will be compared using Gray’s test. The subdistribution hazard ratio will estimate the treatment effect.Duration of hospital and ICU stay: both parameters will be analyzed as time-to-event parameters with competing risk, whereby the event of interest is discharged from hospital/ICU, and the competing risk is hospital/ICU death.Continuous normally distributed variables (e.g., QTc) will be analyzed using a 2-sample *t* test. Treatment effects will be estimated by the difference in mean values between the groups. If applicable, changes from baseline will be calculated. Comparisons between treatment groups will be made by performing an analysis of covariance (ANCOVA) on the post-baseline value, using the baseline value as a covariate.Continuous non-normally distributed variables (clinical status, NEWS score, duration of supplemental oxygen, duration of mechanical ventilation) will be analyzed using a Wilcoxon rank-sum test. Change in ordinal scale at specific time points will be compared using Wilcoxon rank-sum tests.The proportion of patients with D-dimer < 1000, ferritin < 1000, and LDH < 600 on day 6 and day 15 will be compared.The proportion of patients who develop hyperinflammation at days 3, 6, and 15; time to hyperinflammation.

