### Methods for additional analyses (e.g., subgroup analyses) {20b}

To evaluate the effect of aprotinin and high-dose enoxaparin vs. anakinra, analyses will be performed separately in patients with or without signs of hyperinflammation at randomization (i.e., with or without an indication for anakinra in the intervention group).

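### The lymphocyte threshold that defines hyperinflammation is printed per mL instead of per μL, 1000-fold too low, in both places where it appears

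*Protocol article*

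**What the plan says.** Trial design {8} of the protocol article gives the rule for adding anakinra in the intervention arm: "Hyperinflammation is defined as an absolute lymphocyte count < 1000 cells/mL and two of the following". The three other markers are ferritin above 800 ng/mL, LDH above 400 U/L and D-dimers above 1000 ng/mL. The section Treatment of hyperinflammation repeats the definition with the same lymphocyte unit and lists the lymphocyte count as a separate item beside the two-of-three rule. In both places the lymphocyte condition is therefore mandatory.

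The definition has three uses:

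- **Treatment.** Laboratory tests are evaluated daily, and according to Strategies to improve adherence to interventions {11c}, "some patients will be started on anakinra when criteria are met".
- **Separate analyses.** To distinguish aprotinin plus higher-dose LMWH from anakinra, Analysis of the primary efficacy endpoint splits patients "with or without an indication for anakinra in the intervention group". Methods for additional analyses {20b} says that "analyses will be performed separately in patients with or without signs of hyperinflammation at randomization".
- **Secondary endpoint.** Analysis of the secondary endpoint(s) lists "The proportion of patients who develop hyperinflammation at days 3, 6, and 15; time to hyperinflammation".

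**The concern.** The criterion "absolute lymphocyte count < 1000 cells/mL" describes a near-total absence of circulating lymphocytes. It is not the moderate lymphopenia that one would expect as a prognostic marker in hospitalized COVID-19 patients. Because the condition is joined to the other markers by a logical AND, no combination of ferritin, LDH and D-dimer values can make up for it.

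The threshold decides who receives an investigational drug (anakinra 400 mg per day intravenously for 15 days), who falls into which analysis subgroup, and when a secondary endpoint event occurs. A flag programmed exactly as printed would put nearly every patient in the group without hyperinflammation and leave the other group empty. The sites use their own laboratories for routine tests, so the unit matters when results are mapped to a derived variable.

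**Working it through.** **Inputs from the protocol article**

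- Lymphocyte threshold: below 1000 cells/mL (Trial design {8}; Treatment of hyperinflammation).
- The article's other blood-cell threshold: platelets below 30,000 per μL (Exclusion criteria).
- Planned numbers: 60 patients in the pilot, 210 in total (Sample size {14}).

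**Unit conversion (exact)**

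- Printed: 1000 cells/mL ÷ 1000 μL/mL = 1 cell/μL = 0.001 × 10^9/L.
- Evidently intended: 1000 cells/μL × 1000 μL/mL = 1,000,000 cells/mL = 1.0 × 10^9/L.
- Ratio: 1,000,000 ÷ 1000 = 1000.

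Counts of 200, 500 and 800 cells/μL equal 200,000, 500,000 and 800,000 cells/mL. All three fail the printed criterion and meet the corrected one.

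**Internal evidence for the intended unit**

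- The platelet criterion is per μL. The μ survives there, so a fault in reading the PDF is an unlikely explanation for the same wrong unit in two separate sections.
- Treatment of hyperinflammation presents these laboratory values as independent predictors of adverse outcome in severe COVID-19. A value that practically never occurs could not have been identified as one.
- Section {11c} expects some patients to start anakinra, and the separate analyses presume that both subgroups have members.

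**Illustration of the consequence (assumed distribution)**

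The article gives no lymphocyte distribution. Assume lognormal counts with a median of 300 to 1500 cells/μL and a log-SD of 0.4 to 1.0. Then P(count < c) = Φ((ln c − ln median) / log-SD).

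| Median (cells/μL), log-SD | c = 1/μL (as printed) | c = 1000/μL (intended) |
|---|---|---|
| 300, 1.0 | Φ(−5.70) = 5.9e-9, the largest in the range | not an extreme of the range |
| 300, 0.4 | smaller than 5.9e-9 | 0.999, the largest in the range |
| 800, 0.5 | 4.6e-41 | 0.67 (about 40 of 60; 141 of 210) |
| 1500, 0.4 | 5.7e-75 | 0.155, the smallest in the range (about 9 of 60; 33 of 210) |

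At most, the printed threshold gives 210 × 5.9e-9 = 1.2e-6 expected patients. Even 16 daily measurements per patient would raise this only to about 16 × 1.2e-6 = 2e-5. The intended threshold gives 16% to over 99% of patients. These figures are for the lymphocyte condition alone, before the two-of-three requirement.

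**The case against.** The strongest objection is that this is a one-character slip with an obvious reading. Staff evaluate laboratory tests daily under drug-specific SOPs, with investigators on call at all hours. A literal reading would mean that anakinra is never given, which would soon be noticed. The operative document is the full protocol (version 2.1), which is not shown and may carry the right unit, so no effect on conduct or analysis is demonstrated. The lognormal model is not taken from the article, its extreme-tail values mean nothing at that precision, and the range under the intended unit is too wide to inform planning. The intended unit is itself an inference.

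Much of this stands. The practical risk is limited, and the empty subgroup and missing events arise only if the text is applied as printed. The tail probabilities should be read as *effectively zero* and no more; the exact factor of 1000 carries the point. The inference to per μL is strong but should be confirmed.

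The objection does not remove the error. The article does not leave the threshold to another document: it states it twice, wrongly, and nothing in the article corrects it. The threshold is also a decision rule for treatment and analysis, so a reader who follows the text gets a wrong result.

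**Conclusion.** The concern holds: the criterion is wrong as written and should be fixed. The printed lymphocyte threshold is 1000-fold below the evidently intended one. That factor is exact and rests only on the inference that cells/μL was meant. Under any assumption in the stated range, a literal reading lets practically nobody meet the definition.

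The error reaches the anakinra trigger, the analyses with and without hyperinflammation, and the secondary endpoint of developing hyperinflammation and the time to it. It does not reach the pilot D-dimer endpoint, the primary endpoint, sample size, power or alpha. The presentation of outcomes "separately for patients with mild/moderate vs. severe disease at baseline" and the other biomarker proportions among the secondary analyses are also unaffected.

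**What to change.** In Trial design {8} and in Treatment of hyperinflammation, change the lymphocyte unit to cells/μL, preferably adding the equivalent < 1.0 × 10^9/L so that the value cannot be misread. Confirm it against the full protocol (version 2.1), the eCRF and the units reported by each site laboratory. Use this one definition for the anakinra trigger, for the subgroup flag in Analysis of the primary efficacy endpoint and in {20b}, and for the hyperinflammation secondary endpoint.

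The cost is a unit correction in two places and a short check of three sources. The design and the sample size do not change.

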**Fig. 2 Fig2:**
[figure not shown]
Trial design

DAWN-AntiCo will start with a pilot phase powered to detect the biochemical response and will continue to detect the effect on clinical outcomes. In this trial, a superiority hypothesis will be tested with a two-sided type I error rate of 0.05. Secondary hypotheses will be tested in a non-hierarchical way. The statistical analysis plan will be finalized before the database lock.

## Methods: participants, interventions, and outcomes

### Study setting {9}

Study participants will be recruited from different hospitals in Belgium: the University Hospitals Leuven, Ziekenhuis Oost-Limburg Genk, and GZA Hospital Group Antwerp.

### Eligibility criteria {10}

In short, participants eligible for inclusion are hospitalized, adult patients with confirmed and severe COVID-19. Exclusion criteria are both general and drug-specific. Inclusion and exclusion criteria are summarized below; the fully detailed criteria are listed in the appendix.

#### Inclusion criteria

Male or non-pregnant female adult ≥ 18 years of age at the time of enrolmentConfirmed diagnosis of SARS-CoV-2 infection, defined as *either*:
SARS-CoV-2 PCR positive within 72 h before randomization*or*Respiratory infection symptoms (fever, cough, dyspnea, desaturation) and typical findings on chest CT scan and absence of other plausible diagnoses.In patients without PCR-confirmed diagnosis at inclusion, all efforts will be made to confirm definite SARS-CoV-2 infection (e.g., PCR on bronchial aspirate, PCR on BAL fluid or serologic testing). Participants who—despite all efforts—do not have a confirmed diagnosis of COVID-19 will be excluded from the analysis.Illness of any duration and at least one of the following:
Radiographic infiltrates by imaging (chest x-ray, CT scan, etc.) *or*b.Clinical assessment (evidence of rales/crackles on lung auscultation) ANDSpO2 ≤ 94% on room air *or*c.Requiring mechanical ventilation and/or supplemental oxygen.

